# 1. Introduction

## 1.1 Background

Chronic pelvic pain (CPP) is pain of >6 months duration that is severe enough to cause functional disability or require medical or surgical treatment [1]. CPP includes a variety of pain symptoms including dysmenorrhea (pain during the menstrual period) , dyspareunia (pain on sexual intercourse), dyschezia (pain and difficulty with bowel movements) and dysuria (pain on urination), as well as pelvic visceral or muscle pain [2]. Worldwide prevalence rates are between 5.7% and 26.6% [3], affecting approximately 176 million women worldwide. CPP affects more than 70% of Australian women during their reproductive lifespan, most commonly with dysmenorrhea but 21.5% experience non-menstrual pelvic pain and 14.1% experience dyspareunia [4]. Endometriosis is the presence of endometrial tissue outside the uterus and the most common causes of CPP[5] with between 24% to 40% of women with CPP having diagnosed endometriosis [2, 6]. In addition to the CPP symptoms, 30-50% of women with endometriosis have impaired fertility [7]. A number of mechanisms are posited for the development of endometriosis[5], including over expression of PGE2, increases in nerve growth factor (NGF) and both central and peripheral sensitization (allodynia) [8]. Current treatments such as non-steroidal anti-inflammatories, oral contraceptive pills and hormonal treatments have limited efficacy [9] and the side effect profile is bothersome with discontinuation rates of 25-50% [10]. Surgical interventions are costly and invasive, and recurrence rates for pain are high, with 50% of women having pain recurrence at 5 years post-surgery [5, 9].

*Acupuncture*

Complementary and Alternative medicine (CAM) is commonly used by women in Australia with chronic pelvic pain, with an acupuncturist being the most common practitioner visited [11]. Acupuncturists in the community also reporting commonly seeing women with endometriosis [12]

There is little high quality evidence for using acupuncture in the treatment of endometriosis [13] however two recent studies have shown significant promise in reducing endometriosis related CPP using a short course (10-16 treatments) of acupuncture. One trial [14] found clinically significant reductions in VAS pain scores (-5.4 vs -1.2) and one trial [15] a reduction in a numerical rating scale (NRS) for pain (MD -1.4, 95% CI -2.6 to -0.2). Both trials compared acupuncture to different styles of sham acupuncture. However both trials suffer a number of methodological issues such as very small sample sizes [15], less common Japanese style of acupuncture [15] or the use of a cross-over design [14] which may not be appropriate in trials of acupuncture for cyclical pain issues. Acupuncture has multiple mechanisms by which it may reduce endometriosis related CPP including the potential to reduce PGE2 expression [16] reduce NGF [17], increase endogenous opioid release [18] and reduce mechanical allodynia [17].

*Neurological and biomarkers in Endometriosis related Chronic Pelvic Pain:*

Using neurological or biomarkers in conjunction with clinical outcomes has the potential to fill a significant gap in our current knowledge on acupuncture’s potential mechanism(s) of action and is a key area for acupuncture research according to a recent whitepaper written by the Society for Acupuncture Research (SAR) [19]. Interleukin-6 (IL-6) is a cytokine and inflammatory marker implicated in the pathogenesis of endometriosis[8]. Serum IL-6 levels are raised in women with endometriosis [20, 21], and, are positively correlated with disease stage [22] and change in response to symptom severity during treatment [23]. Acupuncture has been shown to reduce IL-6 levels [16, 17]. To date there has been one small study that has examined the effect of Japanese acupuncture vs sham acupuncture on IL-6 in women with endometriosis but due to severe recruitment issues the study was underpowered to detect any differences between groups [24]. Therefore acupuncture’s effect on IL-6 in endometriosis remains unclear.

Neuroimaging has shown a correlation between endometriosis related CPP, depression and anxiety, and increased connectivity between the anterior insula and medial prefrontal cortex [25]. A recent systematic review demonstrates acupuncture has the ability to regulate this pain-related functional connectivity [26] but no measurements of acupuncture’s effect on functional connectivity in women with CPP have been undertaken. Electroencephalography (EEG) is a simple, low cost way to investigate this connectivity[27]. Dysfunctional endogenous pain inhibition is also commonly found in chronic pain conditions [28] however its presence in endometriosis related CPP has not yet been demonstrated. Conditioned pain modulation (CPM) is a technique to investigate individual differences in pain inhibition in women with CPP. This study will explore changes in pain processing in women with endometriosis via changes in default network connectivity or endogenous pain modulation and the effect, if any, of acupuncture on these two possible mechanisms examined.

## 1.2 Study Rationale

Acupuncture is a low-risk treatment [29] and shows promise in treating some of the physiological mechanisms underlying the pathogenesis of endometriosis while preliminary clinical trials have shown clinically significant analgesia. There is only preliminary data on the feasibility of using IL-6, EEG and CPM as objective markers of changes in inflammation and central pain processing in women with CPP. In fact, we have no data on the clinically important difference in reducing pain from endometriosis to guide the design of an appropriately powered randomised controlled trial. These are vital components that need to be understood prior to embarking on a fully powered randomised controlled trial.

# 2. Study Objectives

The aim of this study is to (1) assess the feasibility and acceptability of acupuncture and (2) to investigate any changes in neurological or biomarkers when using acupuncture to treat endometriosis-related chronic pelvic pain.

The specific objectives are (1) To determine barriers to recruitment, appropriateness of eligibility criteria, acceptability and adherence to treatment in women with endometriosis related CPP. (2) To determine the minimal clinically important reduction in pain from endometriosis (3) To determine which, if any, objective markers of endometriosis CPP are altered by acupuncture (4) To determine if the endogenous pain modulation system is affected in women with CPP.

# 3. Study Design

A randomised controlled feasibility trial comparing acupuncture plus usual care to usual care alone for women with endometriosis related CPP.

# 4. Study Population

## 4.1 Sample Size

30 women in total, 15 participants per group.

## 4.2 Recruitment

We will recruit from the community using a patient support group Endometriosis Australia’s, Endoactive and The Pelvic Pain Foundation of Australia and social media portals. We will also recruit via Facebook advertisement for women aged 18-45 living within a 40km radius of Campbelltown, New South Wales, Australia.

## 4.3 Inclusion Criteria

- Women aged 18-45
- have a laparoscopic diagnosis of endometriosis in the last 5 years as per current clinical guidelines [30-32]
- having regular menstruation
- the presence of at least one of the following: dysmenorrhea, dyspareunia, dyschezia or dysuria rated >= 4/10 on a numeric rating scale.

## 4.4 Exclusion Criteria

## endometriosis surgery within the past 6 months,

## started oral or injectable contraceptive pill, GnRH-a or danazol within the last 6 months.

# 5. Participant selection and enrollment

## 5.1 Identifying participants

Recruitment will be primarily via Endometriosis Australia, Endoactive and Pelvic Pain foundation of Australia, all not for profit charities. Trial information and invitations to participate will be published on their respective websites as well as via their Facebook pages and twitter feeds. Recruitment will also occur via targeted Facebook advertising

5.2 Screening for eligibility:

For women expressing interest in the study they will make contact with the co-ordinating centre. Initial screening will be undertaken over the phone by the researcher. For those women that pass the initial screening, they will be invited to fill in a daily pain diary for four weeks to confirm eligibility and to provide baseline pain data.

To participate in the EEG sub-study women need to not meet any of the following criteria:

- Diagnosed psychiatric disorders including: dissociative disorder, obsessive-compulsive disorder, personality disorder, schizophrenia, bipolar disorder
- History of drug and alcohol dependence or substance-related disorders
- History of seizures
- Head trauma with loss of consciousness
- Left-handedness

If women meet any of these criteria they will not have EEG measurements performed but all other components of the study remain the same.

## 5.3 Consenting participants

For those that consent a trial entry form will record baseline clinical data as well as demographic characteristics. Randomisation will occur after baseline data has been collected.

## 5.4 Ineligible and non-recruited participants

Women who do not meet the initial eligibility criteria will be logged. Women who decline to participate after initial contact will also be logged, with a reason for declining (if given). Women who meet the trial inclusion criteria but cannot participate in the EEG sub-study will be logged with reasons for exclusion from the sub-study.

## 5.5 Randomisation

5.5.1 Randomisation

**Sequence generation**

The randomisation sequence will be created using the random number generator in SPSS by a researcher external to the research team. This researcher will hold the randomisation sequence.

**Allocation concealment**

PI [name] will call the central telephone number for treatment allocation once the participant has been enrolled in the study. Once known, PI [name] will communicate the group allocation to the participant.

5.5.2 Treatment allocation

Randomization will be 1:1 into one of two study groups:

Manual acupuncture + usual care:

Women in this group will receive 16 acupuncture treatments over 8 weeks (twice weekly – with a minimum of 2 days between treatments) in addition to their usual care, delivered by registered Chinese medicine practitioners in private clinics or at the clinic room (5.LG.07) at the National Institute for Complementary Medicine. Manual acupuncture will be delivered using a semi-standardized protocol based on previous research [14, 33].

Usual care:

Participants will continue with the usual care as currently prescribed or advised by either their general practitioner or gynecological specialist. Usual care will be based on specific medical advice that has been given to the participant, but commonly involves the oral contraceptive pill or non steroidal anti inflammatories or analgesic medication.

5.5.3: Withdrawal procedures

If a participant wishes to withdraw from the trial they will be immediately removed from treatment.

If a participant withdraws during intervention they will not be replaced however if they withdraw post randomization but prior to the first treatment they will be replaced.

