# 6. Investigational therapy and controls

## 6.1 Acupuncture

A total of 16 treatments over 8 weeks will be administered (2/week). All study acupuncturists will be experienced, with a minimum of a Bachelors level qualification in Acupuncture and will hold current Chinese Medicine practitioner registration with AHPRA. Practitioners will be located in central and western Sydney areas. The PI ([name]) is also an acupuncturist and will train the practitioners in the trial protocol as well as delivering treatments to those women who find treatment at Campbelltown campus geographically conveneient.

Acupuncture treatment will be delivered via a fixed set of acupuncture points, based on those used in a previous pilot clinical trial using a traditional Chinese medicine (TCM) framework to treat endometriosis [14]. Acupuncture points will include Spleen 6, Spleen 8, Spleen 10, Stomach 29, Stomach 36, Ren 3, Ren 4 and Liver 3.

Acupuncture points will be needled bilaterally and needles retained for 25-30 minutes. Point location and needling depth will be as specified in *A Manual of Acupuncture* [34]. Single use, stainless steel needles of varying gauge (.20 x 30mm or .25 x 40mm), dependent on body shape, will be used.

No other TCM co-interventions (moxabustion, cupping or herbal medicine) will be allowed during the trial.

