# 7. Study Assessments

## 7.1 Safety Assessments

At each treatment session the treating acupuncturist will ask the participants if they have had any adverse events or reactions after the last treatment. Any adverse events or reactions that are thought to be causally associated with the intervention will be recorded in the practitioners log book and reported to the primary investigator [name]. Any adverse events reported to the PI will be discussed with the other investigators for clinical significance. All adverse events reported during the duration of the trial will be recorded under adverse events as part of the case report form.

Minor adverse events for acupuncture are expected to occur at a rate of around 8.6% however these were mostly minor with 2.2% requiring treatment [35]. The most common adverse events were minor bleeding or hematoma (6.1%) and pain (1.7%). Negligence or malpractice accounted for .1% of all adverse events and included broken or forgotten needles or pneumothorax. Bleeding and hematoma made up 58% of all adverse events. Neither of the two pneumothorax that occurred were life threatening. No deaths or permanent injuries were associated with the acupuncture treatments.

EEG is non-invasive research, so there is very minimal discomfort involved. It is possible that there may be a very small amount of discomfort when the electrode cap is fitted on participants' heads. The researcher will do everything possible to ensure that this experience is as comfortable for participants as possible. This will be done by ensuring that your cap is the correct size, and the researcher will check with participants throughout the experiment to ensure that the cap remains comfortable.

Participants will also be asked to provide a blood sample. The sample will be collected by a trained phlebotomist, and discomfort will be very minimal.

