Participants will undergo a conditioned pain modulation test to measure the function of their descending pain systems. This test involves applying pressure stimuli to one part of the body while another part of the body is experiencing heat or cold pain. In this study we will be applying stimuli to the volar surface of the forearm. There are no risks associated with pressure stimuli. Some discomfort may be present when the pressure sensation first changes to one of pain. However, as this is a threshold test, the pressure stimulus will be ceased as soon as the participant notes that the sensation has changed from pressure to pain. There is a small risk of a burn with any application of heat. The risk of a burn will be reduced by screening and excluding participants with reduced peripheral sensation. In the unlikely event of a burn, standard operating procedure for treatment of a burn will be implemented. All staff will be familiar with these procedures.

The EEG, conditioned pain modulation and blood samples will all be taken during a single session at the same location at the National Institute of Complementary Medicine prior to receiving any trial intervention. This will be repeated at the conclusion of the trial intervention, or after 8 weeks in women who are allocated to usual care.

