## 7.2 Study assessments

Key outcomes will be assessed at baseline and at the end of the intervention. Drawing of blood (IL-6) and neurological investigations (EEG and CPM) will be undertaken. Pain outcomes will be based on daily numeric rating scale (NRS) for non-cyclical pelvic pain and a separate NRS for menstrual pain. The Clinical Global Improvement (CGI) scale and The Endometriosis Health Profile (EHP-30) [36] will be used as secondary quality of life outcomes. Financial and personal impact of endometriosis will be collected via the ENDOCOST questionnaire [37]. Data will also be collected on safety and expectation (using the EXPECT questionnaire).Daily data on rescue medication use, presence and severity of other endometriosis symptoms (dyspareunia, dyschizia, dysuria) will be collected on the daily pain diary. Feasibility outcomes will include an assessment of interest to participate in the trial, identification of appropriate recruitment strategies, the appropriateness of eligibility criteria, compliance with treatment attendance and data collection, and dropout rates.

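### No adverse-event enquiry is scheduled after a woman's last attended acupuncture session, and no reason is recorded at withdrawal, so a reaction that keeps her away is captured only if she volunteers it

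*Protocol*

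**What the plan says.** Protocol 7.1 (Safety Assessments) gives the only adverse-event question with a stated time: "At each treatment session the treating acupuncturist will ask the participants if they have had any adverse events or reactions after the last treatment". The same section provides for reports however they arrive: "All adverse events reported during the duration of the trial will be recorded under adverse events as part of the case report form".

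Protocol 5.5.3 (Withdrawal procedures) says "If a participant wishes to withdraw from the trial they will be immediately removed from treatment", followed by a rule on who is replaced. It mentions no exit question, reason or safety contact.

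The EEG, pain-modulation and blood session held before treatment is repeated at the end. Section 7.1 says: "This will be repeated at the conclusion of the trial intervention, or after 8 weeks in women who are allocated to usual care". It attaches no adverse-event question to that session.

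Section 7.2 says that safety data will be collected, without a time or method. Its feasibility outcomes include "compliance with treatment attendance and data collection, and dropout rates". Section 5.4 logs reasons for women who decline after first contact and for those excluded from the EEG sub-study. No section asks for the reason when a randomised woman stops.

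**The concern.** The question in 7.1 looks backwards and depends on the woman attending again. Each interval between sessions is covered by the next session, except the last, which has no next session. For most women that interval is like any other. For a woman who stays away because of a reaction after she left the clinic, it is the interval that contains the reaction. Reactions that women tolerate are asked about, while one that ends attendance depends on a spontaneous report.

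Two things are at stake. The acupuncture arm's harm data could be incomplete in one direction, towards too few events. And a dropout count without reasons cannot separate women who stopped because of harm from those who found two visits a week too much. Objective 1 asks about acceptability and adherence, so that distinction is part of what the trial is meant to learn.

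**Working it through.** The plan states no figure for adverse-event coverage, so there is none to reproduce. The check has two parts.

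**1. Is the question asked anywhere else?**

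| Place in the protocol | What it provides | Covers the time after the last session? |
|---|---|---|
| 7.1, session enquiry | Question about the time since the previous treatment | No; needs a further session |
| 7.1, case report form | Records events that are reported | Only if a report is made |
| 7.1, end session | EEG, pain modulation, blood | A contact, with no adverse-event question |
| 7.2 and 8 | Safety data to be collected; the daily diary lists pain, rescue medication and symptoms | No time or method given for safety |
| 5.5.3 | Removal from treatment; replacement rule | No |
| 10.1 | Team meetings and practitioner contact on retention, follow-up and reported events | Not a question to the woman |
| 11.2.2 | Emergency numbers | Spontaneous reports only |

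None of these schedules an enquiry for that interval.

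**2. How large is the gap?**

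Inputs: 15 women per group (4.1, "30 women in total, 15 participants per group") and 16 sessions over 8 weeks (6.1). An interval is the time that follows one attended session.

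*Full attendance*
- Intervals: 15 × 16 = 240.
- Followed by another session, so asked about: 15 × 15 = 225.
- Not followed by another session: 240 − 225 = 15, which is 15/240 = 6.25%.
- All 15 belong to completers, who have the end session. One question there would cover all of them up to the day of that visit.

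*Some women stop* (assumption: 3 of 15 stop after session 4 and do not return)
- Intervals: 12 × 16 + 3 × 4 = 192 + 12 = 204.
- Without a scheduled question: 15. Of these, 12 belong to completers who still have the end session.
- Possibly without any later contact: 3/204 = 1.5%.

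*For one woman who stops after session k and does not return*, the share of her intervals without enquiry is 1/k: 100% at k = 1, 25% at k = 4 and 12.5% at k = 8.

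**Scale of the safety data.** Section 7.1 expects minor adverse events at about 8.6% and does not say per what. If this is read as a rate per woman (an assumption), the expected number of women with an event is 15 × 0.086 = 1.29, and the chance of at least one is 1 − 0.914^15 = 0.74. On that reading one unreported event could be most of the arm's adverse-event data. On another reading of the rate the expected count would differ.

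**The case against.** The strongest reply is that a missing scheduled question does not mean missing data. Section 7.1 records every event reported during the trial, every woman holds emergency numbers, and the team meets regularly about retention and follow-up. A reaction bad enough to end treatment may be the one most likely to be volunteered. Bleeding, haematoma and pain, the most common events listed in 7.1, can arise during needling with the acupuncturist present. This stands. It rules out saying that such events are never asked about or are lost. It does not supply a question, and a moderate reaction that puts a woman off may not prompt a call to an emergency number.

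Three further inferences are tempting, and the protocol does not support them:

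- *The interval without enquiry is always the one in which she decided to stop.* She may have decided earlier, or for reasons of travel or time. A woman who returns, is asked and then withdraws has been asked.
- *Stopping acupuncture counts as withdrawal and ends follow-up.* Section 5.5.3 concerns a woman who wishes to leave the trial. Nothing there, or in the assessment sections, excludes a woman who merely stops attending sessions from the end assessment.
- *The dropout rate is biased.* The rate itself is to be collected. What is not specified is the reason behind it.

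It may also be said that 15 of 204 intervals overstates the exposure, since 12 of the 15 are followed by a visit. That is right, and 3 of 204 is the fairer figure for possible loss of contact.

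**Conclusion.** The point holds in a limited form. The protocol schedules no adverse-event enquiry for the interval after the last attended session, and no recorded reason at withdrawal. The gap is one interval per woman. For completers an existing visit could close it. For women who do not return there may be no later contact: 3 of 204 intervals if 3 of 15 stop after session 4.

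The share is small. The point matters because, for a woman kept away by a reaction, the missing interval is the informative one, and because with 15 women in the arm single events and single reasons count. The direction, towards too few events, rests on the assumption that some such reactions are not volunteered; the documents neither show nor exclude this. The number who stop and the session at which they stop are also assumptions. The subsection between 11.2.3 and 11.2.5 was not available to me, and I assume that it adds no adverse-event question.

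An analysis plan could not repair this, because it concerns what is asked and when. It is worth changing as a cheap improvement and is not a flaw that undermines the trial.

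**What to change.** 1. In 7.1, add an adverse-event question at the existing end-of-intervention session, covering the time since the last treatment.
2. In 5.5.3, when a woman withdraws and if she agrees to be contacted, record her reason for stopping and any adverse event since her last session.
3. In 7.2, report the reasons for stopping alongside the dropout rate.

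The cost is a few lines in the protocol and case report form, one question at a visit that already takes place, and one short call per woman who stops. Adverse-event counts may come out slightly higher. A woman who refuses contact remains uncovered, and the report should give the number of such women.

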## 6.2 Control group

Participants will continue with the usual care as currently prescribed or advised by either their general practitioner or gynecological specialist. The use of usual care alone will allow the natural progression and fluctuations in CPP to be isolated from the effect of acupuncture.

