# 8. Data Collection

Baseline demographic data on age, ethnicity, menstrual history, smoking, current medication and revised American Society of Reproductive Medicine (rASRM) classification [38] of endometriosis will be collected by the primary investigator ([name]) at prior to the first acupuncture session. Baseline pain scores for both non-cyclical and menstrual pain will be collected prior to trial entry. The EXPECT questionnaire will be used to determine expectancy and belief in acupuncture.

*Primary outcome measure:*

The primary outcome measures are daily 0-10 numeric rating scale (NRS) for non-cyclical pelvic pain and a separate daily 0-10 NRS used for menstrual pain during the period itself.

*Secondary outcome measures:*

The Clinical Global Improvement (CGI) scale and The Endometriosis Health Profile (EHP-30) [36] will be used as secondary quality of life outcomes. Data will also be collected on safety, expectation, rescue medication use, presence and severity of other endometriosis symptoms (dyspareunia, dyschizia, dysuria) as well as the financial and personal impact (e.g time off work, additional help required at home) of endometriosis related symptoms. Feasibility outcomes will include an assessment of interest to participate in the trial, identification of appropriate recruitment strategies, the appropriateness of eligibility criteria, compliance with treatment attendance and data collection, and dropout rates. components of the consultation and treatment sessions were important.

*Quality assurance:*

Quality assurance measures on needling technique will be carried out on practitioners during the study period by using an independent acupuncturist to check point selection and location at least once for each practitioner.

*Biomarkers:*

Drawing of blood (IL-6) will be undertaken by PI [name] at baseline and at completion and neurological investigations (EEG and CPM) will be undertaken at baseline and again at the conclusion of treatment by PI [name] and PI [name].

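### Replacing women who withdraw before a first treatment treats the arms unequally and, if they are not counted, understates non-start and dropout

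*Protocol*

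**What the plan says.** Protocol section 5.5.3 (Withdrawal procedures) sets two rules in one sentence. A woman who leaves once the intervention is under way keeps her place unfilled. For those who leave sooner, the rule is that "if they withdraw post randomization but prior to the first treatment they will be replaced". The dividing line is the first treatment.

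The surrounding sections give the context:

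- Section 4.1 fixes the size: "30 women in total, 15 participants per group". Section 5.5.2 adds: "Randomization will be 1:1 into one of two study groups".
- Section 5.5.2 gives the acupuncture arm a course of trial treatment: "Women in this group will receive 16 acupuncture treatments over 8 weeks". For the control arm, section 6.2 says: "Participants will continue with the usual care as currently prescribed or advised by either their general practitioner or gynecological specialist". No trial treatment is given there.
- Section 5.5.1 (Allocation concealment) has an investigator telephone for the allocation once the woman is enrolled. The investigator then "will communicate the group allocation to the participant".
- Section 8 lists among the feasibility outcomes "compliance with treatment attendance and data collection, and dropout rates", and section 7.2 lists the same items. Section 2 makes acceptability of treatment and adherence to it part of the first specific objective.
- Section 5.4 describes a log of ineligible women, women who decline after first contact, and women excluded from the EEG sub-study. It does not mention women who withdraw after randomisation.

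**The concern.** The rule acts after randomisation, after the woman knows her arm, and on an event that only one arm clearly has. A woman who learns that she must attend twice a week for eight weeks, and leaves before session 1, is giving direct evidence on acceptability. If a willing starter takes her place and she is no longer counted, that evidence is lost and the acupuncture group becomes a selected one. Nothing equivalent is defined for a usual-care woman who leaves because she was not given acupuncture.

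Two things are at stake. The first is the set of dropout, adherence and acceptability figures, which are the main product of this trial and would be used to plan a full one. The second, and lesser, is the comparison between arms. Section 9.2 plans a mixed model ANCOVA for pain and CPM, and section 6.2 relies on the control arm to separate natural fluctuation from the effect of acupuncture. Both need the arms to remain as randomised.

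**Working it through.** **Stated size.** 2 × 15 = 30, which agrees with section 4.1. Section 9.1 says that no sample size calculation was done, so there is no power figure to reproduce. The protocol gives no expected dropout or non-start rate.

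**How the rule reads in each arm.**

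| | Acupuncture | Usual care |
|---|---|---|
| Is there a first trial treatment? | Yes, session 1 of 16 | No |
| Window, if the rule needs a treatment to come | Allocation to session 1 | None: nobody is replaced |
| Window, if the rule is taken literally | Allocation to session 1 | Never closes: any withdrawal could be replaced |

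Section 7.1 gives usual care an equivalent for the end of treatment (8 weeks) but none for its start. The arms are treated differently on either reading.

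**Non-start rate.** Let k be the number of acupuncture women who withdraw before session 1 and are replaced, with the arm ending at 15 starters. Then 15 + k women were allocated to acupuncture, and the true non-start proportion is k/(15 + k). If replaced women are not counted, the figure shown is 0/15. The last column adds an assumed 3 withdrawals during treatment: the apparent dropout is 3/15 = 20.0%, and the true figure is (3 + k)/(15 + k). Both k and the 3 are assumptions.

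| k | True non-start | Shown if uncounted | True total dropout (shown as 20.0%) |
|---|---|---|---|
| 1 | 1/16 = 6.3% | 0/15 | 4/16 = 25.0% |
| 2 | 2/17 = 11.8% | 0/15 | 5/17 = 29.4% |
| 3 | 3/18 = 16.7% | 0/15 | 6/18 = 33.3% |
| 4 | 4/19 = 21.1% | 0/15 | 7/19 = 36.8% |

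**Arm mean.** Suppose leavers and starters differ by D points on the 0–10 pain scale. Leaving the k women out shifts the acupuncture mean by D × k/(15 + k). For an assumed D of 1 to 2 points:

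- k = 1: 1/16 × 1 = 0.06 to 1/16 × 2 = 0.125
- k = 4: 4/19 × 1 = 0.21 to 4/19 × 2 = 0.42

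If nobody is replaced in usual care, that arm has no matching shift.

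**The case against.** The strongest reply is that replacement is only a recruitment rule. No sentence removes replaced women from the participant flow, the dropout figures or the analysis, and the definition of analysis sets is often left to a statistical analysis plan, which is not at hand. This stands in part: exclusion is suggested by replacement with a fixed 15 per group, but it is not stated. It does not clear the rule itself. A trigger that fits one arm only is written into the protocol's conduct section, and an analysis plan could restore the denominators but not remove that trigger.

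Four stronger readings are tempting but are not supported:

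- *Replacement can happen only in the acupuncture arm.* The sentence speaks of a participant in either arm. Taken literally, a usual-care woman is always before a first treatment. What is supported is that her window is undefined.
- *Dropout is hidden.* This follows only if replaced women go uncounted.
- *Every between-arm contrast is biased.* This also depends on exclusion. In addition, section 9.2 assesses IL-6 change with a paired t-test, which is not clearly a between-arm contrast.
- *Concealment is lost.* The protocol does not say that a replacement goes to the vacated arm. Section 5.5.1 has the sequence held by someone outside the team and the allocation released after enrolment, so a replacement could take the next place with concealment intact. The threat arises only if she is directed to a chosen arm.

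It may also be said that this is only a feasibility study. That weakens the point about efficacy comparisons, but it strengthens the point about dropout and acceptability.

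**Conclusion.** The concern holds as a defect in a stated rule. Replacement follows open allocation, depends on an event that only the acupuncture arm clearly has, and comes with no statement of how replaced women are counted. These facts rest on the text alone.

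The size is conditional. If replaced women are left out, and if 1 to 4 acupuncture women fail to start, a true non-start of 6.3% to 21.1% could be reported as zero. The shift in the pain comparison, at most 0.42 points under the assumptions used here, is secondary because the comparison is exploratory. An established break in randomisation or in concealment cannot be claimed from this document.

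**What to change.** In section 5.5.3, remove replacement based on the first treatment. State instead that:

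- every randomised woman stays, under her allocated arm, in the participant flow and in the dropout and adherence denominators, with withdrawals before and after the first session shown separately for acupuncture;
- all randomised women are analysed as randomised wherever outcome data exist;
- if extra women are recruited, one criterion that means the same in both arms decides this, and each takes the next place in the concealed 1:1 sequence, never a chosen arm.

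Extending the log in section 5.4 to withdrawals after randomisation, with the reason where given, would capture the acceptability information. Section 5.3 places randomisation after baseline collection, so baseline data for these women will already exist.

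The cost is a few sentences of protocol text. The number with outcome data may fall slightly below 15 in an arm, or the arms may end slightly unequal. Since section 9.1 makes no power claim, neither weakens a stated design property beyond the nominal 15 per group.
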